## Abstract

**Background::**

To explore the influence of the early path nursing on life quality and the neurological function recovery in the intracerebral hemorrhage (ICH) patients.

**Methods::**

The experiment was implemented from January 2018 to October 2020 at the First Affiliated Hospital of Soochow University. The experiment was granted through the Research Ethics Committee of the First Affiliated Hospital of Soochow University (2017033). In this experiment, the criteria for inclusion includes: hemorrhagic stroke diagnosed via the MRI or head CT; over 18 years of age; patients with motor dysfunction; The Glasgow Coma Scale > 12. The patients with these symptoms will be excluded: severe cognitive impairment; ischemic stroke; onset time > 3 days; and severe complications. The scale used for the evaluation the neurological function is the American Stroke Scale. This scale contains a total of eleven items, that is, the movements of upper and lower limb, the consciousness level, gaze, visual field, etc. Other outcomes include patient satisfaction and complications.

**Results::**

Evaluation the neurological function and quality of life will be shown in Table 1.

**Conclusion::**

The early path nursing can promote the neurological function recovery in the ICH patients.

**Trial registration number::**

researchregistry6327

## Introduction

1

Stroke is the second major cause of death and one of the main causes of disability in the world.^[1–3]^ As life expectancy increases, the stroke burden worldwide is likely to increase, especially in the low-income and middle-income countries.^[4,5]^ Stroke seriously endangers the health and lives of people, and imposes a heavy and huge mental, economic and material burdens on the patients, their families and society.^[6,7]^ Intracerebral hemorrhage (ICH) is the second most prevalent stroke subtype after the ischemic stroke, accounting for about 10% to 20% of all the strokes.^[8,9]^ ICH will occur when the blood vessels in brain parenchyma ruptures.^[10,11]^ ICH can occur in a pre-existing disease complication, for instance, tumor and vascular malformation, and then is called secondary ICH. In the past several years, with the continuous progress and development of medical science, the pathology and etiology of the ICH have been deeply explored. Nevertheless, the nursing care quality remains the key factor affecting the outcomes of ICH.^[12,13]^ Clinical pathway is a concrete process and a kind of standardized work.^[14,15]^ In the nursing process, our department staff develops, adjusts and implements the nursing plans for ICH patients through the rehabilitation teachers and responsible nurses. The personalized nursing plans can improve the rehabilitation outcome and the compliance of patient, as well as make the nurses more reliable in work process. Currently, the early path nursing has seldom been used in the care of patients with ICH. Therefore, we conduct this randomized controlled study protocol to explore the influence of the early path nursing on life quality and the neurological function recovery in ICH patients.

## Methods

2

The experiment was implemented from January 2018 to October 2020 at the First Affiliated Hospital of Soochow University. The experiment was granted through the Research Ethics Committee of the First Affiliated Hospital of Soochow University (2017033) and recorded in research registry (researchregistry6327). Before the registration, the patients who are recruited receive written informed consent. Sequence of random numbers is generated by a computer. Sequentially numbered sealed opaque envelopes are used for the concealment of random numbers. All the patients participating in this study are randomly divided into control group and nursing group, with 30 patients in each group.

### Inclusion and exclusion criteria

2.1

In this experiment, the criteria for inclusion includes: hemorrhagic stroke diagnosed via the MRI or head CT; over 18 years of age; patients with motor dysfunction; The Glasgow Coma Scale > 12. The patients with these symptoms will be excluded: severe cognitive impairment; ischemic stroke; onset time > 3 days; and severe complications.

### Early path nursing

2.2

The patients in both groups are given the routine care. In nursing group, the patients also receive path-based intervention of early rehabilitation nursing. The specific intervention method includes: Intervention time: The patient will be assessed within twenty-four hours after the admission by the medical personnel and nursing staff in charge of the ward. It primarily contains the neurological and physical situations, and the mobility. Meanwhile, medical personnel have set the treatment target and rehabilitation target. Rehabilitation exercise: The rehabilitation training is conducted on the basis of the path chart. On the first day, a detailed assessment of physical function is performed and the patient is assisted in joint activity and physical movement in bed. On the second day, the major task is to teach patient how to turn over. During the process of training, therapists tell the patient to focus on the physical experience and focus on their learning. On the third day, therapists conduct the training of sitting balance and emphasize the cultivation of the self-care ability of patients. On the fourth day, the condition of patient requires to be assessed. It primarily involves the limb flexibility, and the muscle tone and strength of patients. In this exercise, when you are sitting, you need to lean your torso forward, move your center of gravity to the front foot, and the weight is done through the patient's legs. The 5 to 7 days are primarily for the training to stand. Let the patient's feet apart, as wide as the shoulders, and then swing the body to the left and right, mainly to move the center of gravity to the affected side. This process requires attention to protect the patient's knee joint. On the eighth day, muscle tone and strength, and the physical activity of patients are observed. Adjust the treatment approaches appropriately, and then carry on the resistance training of lower limb. From day nine until discharge, focus on the assessment of the motor function of patients and offer some necessary guidance. The responsible nurses should conduct the assessment of daily of patients and take the individualized rehabilitation measures. The rehabilitation therapist implements the weekly consultations on the condition of patients and gives guidance.

### Outcomes

2.3

The scale used for the evaluation the neurological function is the American Stroke Scale. The scale includes eleven items, namely the level of consciousness, upper and lower limb movements, visual field, gaze, and so on. Other outcomes include patient satisfaction and complications.

### Statistical analysis

2.4

The analysis of all the data are conducted with the software of IBM SPSS Statistics for Windows, version 20 (IBM Corp., Armonk, NY). Data acquired are represented through the proper features, e.g. standard deviation, and mean, median as well as percentage. And independent t-tests and χ^2^-tests are respectively utilized to analyze the categorical variable and continuous variable. When *P* < .05, the efficacy is viewed to be statistically significant.

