## Result

3

Evaluation of the neurological function and quality of life will be shown in Table 1.

**Table 1 T1:** Evaluation the neurological function and quality of life between two groups.

	Nursing group (n = 30)	Control group (n = 30)	*P* value
American Stroke Scale			
Length of hospital stay			
Total cost			
Complications			
Quality of life			

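### The stated analysis gives the baseline stroke-scale score no role; baseline-adjusted ANCOVA would be more precise than the planned unadjusted t-test with 30 patients per arm

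*Protocol article*

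**What the plan says.** All statements are in the Protocol article.

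- **Statistical analysis (2.4).** The only tests named are these: "independent t-tests and χ^2^-tests are respectively utilized to analyze" categorical and continuous variables, in that order. At P < .05, "the efficacy is viewed to be statistically significant". No covariate, change score or model is named. Read literally, the sentence pairs t-tests with categorical variables and χ² tests with continuous ones. I take the evident intent, a t-test for the stroke-scale score; the reversed wording is a separate error.
- **Result (3), Table 1.** The shell has a column for each group and one for the P value. There is a single row for the "American Stroke Scale", with no baseline row, change row or between-group difference.
- **Outcomes (2.3).** The scale and its eleven items are introduced without an assessment time.
- **Methods (2).** Patients are "randomly divided into control group and nursing group, with 30 patients in each group". On the allocation list, the text says "Sequence of random numbers is generated by a computer"; no stratification by severity is described.
- **Inclusion and exclusion criteria (2.1).** Entry requires adult age, motor dysfunction and "The Glasgow Coma Scale > 12"; onset more than 3 days earlier is an exclusion.
- **Early path nursing (2.2).** The one early neurological assessment appears in the description of the nursing group's intervention: "The patient will be assessed within twenty-four hours after the admission by the medical personnel and nursing staff". No scale is named for it and it is not tied to the analysis.
- **Introduction (1).** The aim is framed as recovery of neurological function.

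**The concern.** Recovery implies a starting level. A two-group t-test on a single score per patient leaves between-patient differences in starting severity in the error term. The coma-scale criterion narrows the level of consciousness, but an eleven-item scale that also covers limb movement, gaze and visual field can still vary considerably at entry. If the baseline score predicts the later score, using it as a covariate removes part of that variation without adding patients.

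Two things are at stake: the chance of detecting a moderate effect with 30 per arm, and how far the one realised allocation can be trusted if the arms happen to start at different severities.

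**Working it through.** The article gives no effect size, SD, power or sample-size derivation, so there is no stated figure to reproduce.

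**Inputs.** From the article: n = 30 per arm and level 0.05. Assumed: two-sided testing, a true difference of 0.5 SD for the power figures, and a baseline-to-outcome correlation ρ between 0.3 and 0.8.

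**1. Unadjusted t-test.** The standard error of the difference is √(2/30) = 0.258 SD. For 0.5 SD the noncentrality is 0.5/0.258 = 1.94; with 58 degrees of freedom, power is 48% (noncentral t). The difference detectable with 80% power is 0.74 SD.

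**2. ANCOVA.** The residual variance is multiplied by 1 − ρ² and one degree of freedom is lost (57 remain). The standard error is √(2(1 − ρ²)/30), and the equivalent unadjusted sample size per arm is 30/(1 − ρ²).

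| Assumed ρ | 1 − ρ² | Equivalent n per arm | Detectable at 80% power (SD) | Power at 0.5 SD |
|---|---|---|---|---|
| no adjustment | 1 | 30 | 0.74 | 48% |
| 0.3 | 0.91 | 33 | 0.70 | 51% |
| 0.5 | 0.75 | 40 | 0.64 | 59% |
| 0.7 | 0.51 | 59 | 0.53 | 76% |
| 0.8 | 0.36 | 83 | 0.44 | 89% |

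**3. If change scores were tested instead.** The variance factor is 2(1 − ρ). Power at 0.5 SD is then 36%, 48%, 69% and 85% at ρ = 0.3, 0.5, 0.7 and 0.8. This is below ANCOVA throughout, and at ρ = 0.3 below the unadjusted t-test.

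**4. Chance imbalance.** The baseline mean difference also has standard error 0.258 SD. The probability of a gap above 0.25 SD in either direction is 33%; above 0.5 SD it is 5.3%.

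Given a gap b, the unadjusted contrast is shifted by ρb and has conditional standard error √(2(1 − ρ²)/30). The rejection limit is 1.96 × 0.258 = 0.506 SD. By normal approximation:

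- b = 0.5, ρ = 0.5: shift 0.25, standard error 0.224, (0.506 − 0.25)/0.224 = 1.14, conditional type I error about 13%.
- b = 0.5, ρ = 0.7: shift 0.35, standard error 0.184, (0.506 − 0.35)/0.184 = 0.85, conditional type I error about 20%.
- b = 0.25: 4.7% at ρ = 0.5 and 3.6% at ρ = 0.7, so no inflation.

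Averaged over all allocations the error rate is 5%.

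**The case against.** The strongest reply is that this is a condensed article, that covariates are often settled in an analysis plan, and that the named test is valid. Much of that stands, and it limits the point.

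- **A reader might infer that no baseline score is taken, or that the test is on the final score only.** The article says neither. It gives the baseline no role in the comparison, and that is as far as the text goes.
- **A reader might infer that the unadjusted test is biased.** It is not. Under randomisation its overall type I error is 5%, and its standard error already includes chance baseline variation. Imbalance and lost precision are therefore largely the same loss, seen after and before allocation. A gap does not carry over in full either; only the fraction ρ does.
- **A reader might blame the large detectable effect on the missing adjustment.** Most of it comes from having 30 per arm: at ρ = 0.5, ANCOVA still needs 0.64 SD.
- **ρ is unknown.** The entry criteria restrict severity, which tends to lower ρ, and at 0.3 the gain is slight. The article does not establish that the baseline score is the strongest predictor.
- **A reader might say that Table 1 reports P values alone.** It has group columns, and means and SDs are planned, so an unadjusted difference and interval can be derived. An adjusted one cannot.
- **New baseline scores may be unobtainable.** The article gives January 2018 to October 2020 as the trial period.

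What does not stand is that the matter is simply left open. The article names the tests for all the data and lays out the results row, and no other section supplies a baseline-adjusted comparison.

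**Conclusion.** The point holds as a matter of efficiency, not validity. For an aim framed as recovery, with 60 patients and no stratification described, the stated comparison is less precise than a readily available alternative.

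The size of the loss depends on ρ: negligible to small near 0.3 and material from 0.5 upwards, where 30 per arm would act like 40 or more. Protection against imbalance matters mainly in the roughly 1-in-20 allocations with a gap above 0.5 SD; small gaps do no harm to the error rate. These figures assume two-sided testing, an approximately linear baseline-to-outcome relation with common variance, and a baseline score measured alike in both arms. The change is worth making, but the unadjusted result would still be interpretable without it.

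**What to change.** 1. State one fixed time point for the follow-up American Stroke Scale score; ANCOVA cannot be specified without it.
2. State whether a pre-randomisation score was recorded in both arms. Where it was, compare the follow-up score by ANCOVA with that score as covariate.
3. In Table 1, add the baseline score by group and the adjusted mean difference with its 95% confidence interval.
4. If enrolment is complete and controls have no comparable baseline score, adjust instead for age, Glasgow Coma Scale and onset-to-enrolment time, which the entry criteria require to be known for every patient. Say that the gain will probably be smaller, since the coma score can only be 13 to 15 and onset is capped at 3 days; the gains tabulated above do not apply to this fallback.

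The covariates should be fixed before outcomes are compared by arm. The cost is analysis wording and one degree of freedom per covariate, with no extra patients.

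### Efficacy is declared at P < .05 without saying which outcome decides; no outcome is designated primary among five tabulated P values and a two-part objective

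*Protocol article*

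**What the plan says.** The only decision rule is in section 2.4 of the protocol article: at P < .05 "the efficacy is viewed to be statistically significant". The rule does not say which comparison the P value comes from.

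The outcomes appear in three places, and the lists differ:

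- **Objective (Introduction).** The aim is to "explore the influence of the early path nursing on life quality and the neurological function recovery in ICH patients". Quality of life and neurological function stand side by side.
- **Section 2.3, Outcomes.** It opens with neurological function: "The scale used for the evaluation the neurological function is the American Stroke Scale". It then adds: "Other outcomes include patient satisfaction and complications".
- **Table 1, Result.** Under the title "Evaluation the neurological function and quality of life between two groups" there is a P-value column against five rows: American Stroke Scale, length of stay, total cost, complications and quality of life.

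Three table rows (stay, cost, quality of life) are not named in section 2.3. Satisfaction is named in section 2.3 but has no row in the table. The word primary is attached to no outcome anywhere in the article.

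**The concern.** A P < .05 rule holds a 5% error rate for an efficacy claim only if the deciding test is fixed in advance. Here the threshold is fixed and the test is not. A reader of the finished table would see five P values and a rule that could be applied to any of them. Two analysts who both followed section 2.4 could reach opposite conclusions from the same data, one resting on the stroke scale and the other on quality of life.

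The point does not depend on the absence of a multiplicity method, which may properly sit in an analysis plan that is not shown. It concerns a rule that is written down and leaves its own subject open. Which outcome carries the efficacy claim is protocol content, even in a condensed article.

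**Working it through.** The plan has no derived figure to reproduce. The .05 is a threshold, and a single prespecified test has a 5% error rate by definition. The check asks what the rate becomes if the rule is applied to several outcomes.

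**Inputs from the protocol article**
- Threshold per test: 0.05 (section 2.4). Sidedness is not stated; two-sided is assumed.
- Number of outcomes, k: 2 (stated targets, Introduction), 5 (rows of Table 1), or 6 (Table 1 plus satisfaction from section 2.3).

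**Assumptions not in the documents**
- There is no true effect on any outcome.
- Any one P < .05 is taken as efficacy.
- All pairs of outcomes have the same correlation, varied from 0 to 0.9.
- Test statistics are approximately normal, with critical value 1.96.

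**Independent outcomes, either direction:** error = 1 − 0.95^k
- k = 2: 1 − 0.9025 = 9.75%
- k = 5: 1 − 0.7738 = 22.6%
- k = 6: 1 − 0.7351 = 26.5%

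**Independent outcomes, only results favouring nursing:** error = 1 − 0.975^k
- k = 2: 4.9%
- k = 5: 11.9%
- k = 6: 14.1%

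The single-test reference here is 2.5%.

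**Correlated outcomes.** For k = 2 the error is 1 − P(|Z1| ≤ 1.96 and |Z2| ≤ 1.96) from the bivariate normal distribution. For k = 5 and 6 it is the share of 1,000,000 simulated sets of equicorrelated normal statistics with at least one beyond 1.96. Each cell gives either direction / favouring nursing only.

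| Assumed correlation | k = 2 | k = 5 | k = 6 |
|---|---|---|---|
| 0 | 9.8% / 4.9% | 22.6% / 11.9% | 26.5% / 14.1% |
| 0.3 | 9.5% / 4.8% | 20.9% / 10.5% | 24.2% / 12.2% |
| 0.5 | 9.1% / 4.5% | 18.4% / 9.2% | 20.8% / 10.4% |
| 0.7 | 8.3% / 4.2% | 14.8% / 7.4% | 16.4% / 8.2% |
| 0.9 | 7.0% / 3.5% | 10.2% / 5.1% | 10.9% / 5.4% |

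Every cell exceeds its single-test reference (5% or 2.5%). The size of the excess depends mostly on how many outcomes are allowed to count, and then on a correlation that the documents do not give.

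**After the fix.** With one named primary outcome tested at two-sided 0.05, the error rate of the efficacy claim is 5%, or 2.5% in favour of nursing.

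**The case against.** The strongest reply is that the American Stroke Scale is already primary in all but name. Section 2.3 describes it first and calls the rest other outcomes, and the Conclusion speaks only of neurological recovery. No sentence rests an efficacy claim on cost or stay. This carries weight: the lean is real, and it suggests the fix matches the intent. It does not settle the matter, because the objective and the title of Table 1 put quality of life beside the scale, and section 2.4 names neither. Nor is an assessment time or a form of the score fixed for the scale.

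A second reply is that the count of outcomes is inflated. Stay and cost are resource measures, complications are usually read as safety, and satisfaction has no P-value cell. This stands in part. The figure closest to the stated aim is the one for two targets, at most about 10%. The figures for five and six show the limit of what the rule permits.

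A third reply is that the stated aim is to explore. That fits poorly with a rule that declares efficacy by significance.

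Two stronger readings are tempting, and the documents support neither:

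- **The trial's false-claim rate is about 15–26%.** That range needs five or six outcomes, each able to prove efficacy alone and in either direction, with correlation no higher than about 0.7. The article does not state an any-one-wins rule and reports no correlations.
- **The deciding outcome was, or will be, chosen after the data were seen.** The Methods section says in the past tense that the experiment was carried out from January 2018 to October 2020, but it describes recruitment and allocation in the present tense. The Result section says results will be shown, and Table 1 is empty. The article does not say whether outcomes had been seen. That calls for a statement and supports no inference.

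**Conclusion.** The point holds. The written rule ties efficacy to no outcome, so following it does not by itself hold a 5% error rate. If there is no true effect and any one significant result is accepted, the two-sided error is about 7–10% for the two stated targets, 10–23% for the five tabulated outcomes and 11–26.5% for six. Each range runs from an assumed correlation of 0.9 down to independence. In favour of nursing alone, the figures are roughly half these, against 2.5%.

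These are conditional illustrations. What the text establishes without assumptions is narrower: no primary outcome is designated, the decision rule has no subject, and section 2.3 and Table 1 list different outcomes. That is enough to require a change, because it governs whether the trial's main claim can be interpreted.

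**What to change.** In sections 2.3 and 2.4:

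1. Name the American Stroke Scale score as the single primary outcome, at one stated assessment time and in one stated form (final score or change), tested at two-sided 0.05.
2. State that efficacy is claimed only on that test, and that quality of life, length of stay, total cost, complications and satisfaction are secondary or supportive.
3. Reconcile the outcome list in section 2.3 with the rows of Table 1, so that each outcome appears in both.
4. State whether any outcome data had been seen when the primary outcome was fixed. If they had, the choice should be described as made afterwards.

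The cost is a few sentences, with no new data and no change to the conduct of the trial. Naming the scale without its time and form would leave much of the same freedom, so item 1 needs all three parts. How the secondary outcomes are ordered or adjusted can be left to the analysis plan. The real downside is that a lone significant result on another outcome, including quality of life, can no longer be called efficacy.

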## Result

3

Evaluation of the neurological function and quality of life will be shown in Table 1.

**Table 1 T1:** Evaluation the neurological function and quality of life between two groups.

	Nursing group (n = 30)	Control group (n = 30)	*P* value
American Stroke Scale			
Length of hospital stay			
Total cost			
Complications			
Quality of life			

